## Abstract

**Introduction:**

Stroke is the second leading cause of death in Europe. In the case of stroke survival (almost 70%), only 25% of patients recover completely, while the remaining 75% will undergo a rehabilitation phase that varying from months to years. The primary outcomes of a stroke involve motor impairment in the upper limbs, resulting in a partial or complete inability to move the limb on the right or left side, depending on the affected hemisphere. Furthermore, the motor deficit distorts the proprioception of the body and the embodiment ability of the injured limb. This could be rehabilitated through the paradigm of body illusion that modulates the motor rehabilitation. The present protocol aims to investigate the effectiveness of a Virtual Reality system for sensorimotor and proprioception upper limb deficit compared to a traditional upper limb rehabilitation program.

**Method:**

This study has a randomized and controlled design with control and experimental groups, and 4 measurement times: pre-intervention, immediately after the intervention, and two follow-ups (at 6 and 12 months). The inclusion criteria are: (a) Being 18 to 85 years old, both males and females; (b) Suffering from ischemic or haemorrhagic stroke; (c) The stroke event must have occurred from two to eighteen months before recruitment; (d) Patients must have moderate to severe upper limb motor deficit, and the alteration of sensorimotor and proprioception abilities of the injury upper limb; (e) Patients must understand and sign the written consent for enrolment. The rehabilitation last four weeks with three sessions per week at Bellaria Hospital of Bologna (Italy). The VR protocol uses two types of technology: immersive and non-immersive, and the control group follow the traditional rehabilitation program.

## 1. Introduction

According to the European Cardiovascular Disease Statistics, stroke is the second leading cause of death in Europe. It mainly occurs after age 55, with 75% of cases in people over 65 [1]. After a stroke, 20–30% of people die in the first month from the event and 40–50% within the first year. For those who survive, only 25% experience full recovery, with the remaining 75% entering a rehabilitation phase that spans from several weeks to several months or even years. Published randomized control trials that adopted various rehabilitative programs including technology have demonstrated that, at the end of the rehabilitation period, the patient may experience full recovery or remain in a state of permanent disability [2–4].

The primary outcomes of a stroke encompass motor impairment in the upper limbs, leading to a partial or total inability to move either the right or left limb based on the affected hemisphere [5]. In particular, patients experience difficulty performing reaching tasks due to a lack of motor coordination or an inability to control grip and finger strength when manipulating objects [6]. In everyday life, the impairment in the upper limbs manifests as an inability to independently eat, dress, maintain personal hygiene, and engage in other self-care activities, resulting in a reliance on a caregiver. Consequently, consistent rehabilitation to restore motor skills becomes crucial for both the patient and their family members [7].

From a neuroscience standpoint, deficiencies in the planning, preparation, and execution of movements may arise due to impairment in the primary motor cortices or areas responsible for praxis control, particularly those situated in the parietal regions [8–11], which alter proprioceptive and kinaesthetic signals and the perception of peripersonal space [12]. Proprioception refers to the sense of the relative position of one’s own body parts and strength of effort being employed in movement, which can be impaired after a stroke [13]. As a result, patients present distorted body representations and an alteration in the sense of embodiment, in terms of ownership, location, and agency. In particular, people who have survived a stroke experience apparent changes in their bodies, such as altered sensations, impaired limb function, uncoordinated movements and disrupted proprioception [14–16]. Furthermore, sensation, emotions, and perception are some of the characteristics of self-consciousness assimilated into the physical body thanks to the sense of embodiment [17], and that in stroke patients is compromised. The somatosensory deficit that affects this sample of patients refers to an impairment or loss of sensation related to touch, pressure, temperature, or pain on the side of the body affected by the stroke. This deficit occurs due to damage to the brain regions responsible for processing sensory information and patients maintain various delusional beliefs regarding the ownership of their paralyzed limbs [14, 18, 19]. This lack of awareness or recognition of the body can impact the sense of ownership and may lead to difficulties in coordinating movements or adjusting to changes in body perception [20].

Taking into account the concept of neural plasticity, which refers to the brain’s capacity to adapt and facilitate functional activities [21], recent research indicates that intervening with the illusion of the bodily self in hemiplegic patients could enhance the rehabilitation of the affected limb [22, 23]. One of the methods to induce the limb illusion is the mirror box. In this apparatus, the patient sees the reflection of their healthy arm in the mirror, and if the illusion is successfully induced, they perceive the reflected arm as their own instead of the injured one [24]. This process could be possible because the embodiment of the hand reflected by the mirror would improve the reorganization of body representation in patients with post-stroke motor deficits (Tosi et al., 2018). The paradigm of the body illusion was then translated into the Virtual Reality (VR) system [25].

Over the past decades, VR has been widely used in upper limb motor rehabilitation following a stroke, yielding significant results compared to a traditional rehabilitation program [26, 27]. VR is an advanced technology that provides interactive environments that reproduce the surrounding reality. It is divided into immersive and non-immersive systems; the former projects the three-dimensional environment through a Head Mounted Display wear by participants, often incorporate other sensory feedback, such as spatial audio and sometimes haptic feedback, to enhance the feeling of presence within the virtual environment [28, 29]; the latter, on the other hand, projects the virtual environment into a screen and the patient can interact with it through devices such as joysticks or cyber-gloves [30]. Previous literature in the field of post-stroke rehabilitation through VR demonstrated its effectiveness in improving neuroplasticity and motor recovery thanks to several aspects such as real-time feedback, customization of exercises according to the patient’s cognitive and motor abilities, the immersive and interactive experience that the technology offers, and a faithful simulation of real-world activities [31–33]. VR has demonstrated its effectiveness in upper limb rehabilitation, but little is known about how integrating the illusion of one’s limb can benefit rehabilitation. Previous study found that inducing a strong feeling of ownership of a virtual body that could perform movements of any complexity and duration might contribute to restoring motor functions in stroke patients. In this line, a recent systematic review demonstrated the significant modulating role of body ownership illusion through VR to restore motor abilities after stroke [34]. Furthermore, the VR technique can provide interaction between virtual objects and body motion using motion tracking. This technique has proven to be suitable for proprioception rehabilitation due to its ability to manipulate the visual feedback of virtual objects [35]. The VR proprioceptive paradigm is innovative because this type of exercise system cannot be easily provided in traditional therapy. That is, for healthy individuals, the central nervous system integrates multiple modes of sensory information, especially vision and proprioception, to perform motor tasks. In stroke patients, however, the integration of multiple sensory inputs is impaired, and they can only rely on intact visual information rather than somatosensory input [36]. In this case, visual influence becomes predominant when afferent input from other sources is reduced, and the predominant influence of visual input constitutes a natural compensatory strategy for coping with initial stroke damage [37]. According to the theory of neural plasticity cited above, the brain has the ability to reorganize itself by forming new neural connections in response to sensory inputs and repetitive practice [21]. Even if the sensory feedback in VR is an illusion, it can still promote neural plasticity similarly to real sensory signals [38]. For this reason, VR could be an efficacious medium to improve the proprioception abilities and the motor rehabilitation after stroke. However, new study protocols are needed.

Therefore, considering the high incidence of stroke, the disability it entails, and the need for timely and constant rehabilitation, together with the promising data of VR as an effective tool for sensorimotor and proprioceptive rehabilitation, the present project aims to investigate the effectiveness of a VR system for sensorimotor and proprioception upper limb deficit compared to a traditional upper limb rehabilitation program.

## 2. Objectives and hypothesis

Considering the sensorimotor deficits after a stroke and the relate difficulty to build an internal representation of the own body, plus the significative feature of VR to induce a body illusion, the present protocol aims to investigate the effectiveness of a Virtual Reality rehabilitation program to restore the sensorimotor and proprioceptive abilities of the injured upper limb after a stroke, compared with the treatment as usual (TAU). Moreover, the feature of the exergame of VR would engage the patients and motivate them to pursue the rehabilitation program and overcome the drop-out from the rehabilitation.

### 2.1. Hypothesis 1

VR rehabilitation programs will generally be as effective as TAU in increasing the motor abilities of the injured upper limb after a stroke.

### 2.2. Hypothesis 2

The VR rehabilitation program will be more effective than TAU in the proprioception abilities of the injured upper limb.

### 2.3. Hypothesis 3

The TAU will be the least satisfying rehabilitation program for the patient, with a higher probability of abandonment compared to VR.

### 2.4. Hypothesis 4

The same results will be found across the follow-up assessments (6 and 12 months after intervention).

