### 3.5. Outcomes

In assessing the significance of outcome changes, several indicators are utilized. These include the *p*-value, which measures the probability that observed results are due to chance rather than the intervention itself. A *p*-value below a predetermined significance level, often 0.05 or 0.01, indicates statistical significance. Additionally, the confidence interval (CI) provides an estimate of the precision of treatment effects. A narrower CI suggests greater precision in estimating treatment effects. Finally, the Minimal Clinically Significant Difference (MCID) is utilized to assess the significant change perceived by patients regarding the treatment, evaluated through the satisfaction questionnaire.

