#### 3.5.1. Primary outcome

The primary outcome measures will be the Fugl-Meyer for Upper Limbs [45] employed as a performance-based assessment to characterize motor recovery in research, has demonstrated outstanding reliability. This encompasses internal consistency, inter-rater reliability, intra-rater reliability, and test-retest reliability, particularly in the post-stroke context [59]. The assessment includes 33 items to evaluate upper extremity motor impairment and is scored between 0 and 2 (0 = unable, 1 = partly able, and 2 = fully able to complete movement) with a total score range of 0–66. The assessment will be performed before treatment (T1), after the conclusion of the treatment (T2), and after 6 months as a follow-up (T3).

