### 3.7. Statistical analysis

The data analysis follows the Per Protocol approach, that is only participants who have adhered to the study protocol, patients who dropped out of the study are excluded from the analysis. Analysis will be performed through the Statistical Package for Social Sciences (SPSS). Descriptive statistics for both the experimental and control groups will encompass measures such as the mean and standard deviation. The student t-test for independent samples will be used to evaluate the baseline. In case of excessive deviation from normality, a similar non-parametric test (Mann-Whitney) will be used. Changes in motor performance and proprioception between T1 and the subsequent longitudinal evaluations (T2, T3) will be assessed using the repeated measures Analysis of Variance (rmANOVA) with a mixed design 2×3, considering the group as "between subjects" factor and the time point measure as "within subjects" factor. Residual plots will be inspected to verify linearity, normality and homoscedasticity assumptions for all models as well as to identify potential influential outliers. According to the literature, for all inferential analyses the probability of type 1 error is a-priori fixed at alpha α = 0.05 and will include reporting the 95% Confidence Interval for each estimate [62].

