## 4. Discussion

The present protocol describes the background and the design of a study that aims to evaluate the effectiveness of a rehabilitation program with VR in improving sensorimotor and proprioception upper limb ability in patients with stroke. The central hypothesis is that the VR rehabilitation program could increase motor facilitation and, as a consequence, improve upper limb control and function compared to the control condition.

The present protocol was developed because motor impairments are the main consequence of stroke, together with the alteration in body representation and the sense of embodiment that prevent limb movements. Much literature has proven VR’s efficacy in motor rehabilitation after a stroke [26, 27]. However, less is known about the modulating role of the body ownership illusion in eliciting rehabilitation. In this line, a recent systematic review [34] demonstrated the significance of body illusion in promoting motor rehabilitation in patients with stroke, both for the upper [22, 63, 64] and lower limbs [23], compared to the control non-embodied condition. The enhanced feature of the embodied VR system, in contrast to conventional rehabilitation programs like the mirror box [58], lies in its ability to evoke motor imagery using computerized images. Additionally, the patient can receive remote feedback on their training, allowing them to ascertain the correctness of their rehabilitation tasks.

In the present protocol, the VR systems, IVR and HB, permit patients to see their real injured arm projected into the virtual environment, which is immersive for the IVR condition and augmented for the HB condition, stimulating the motor cortex [65, 66]. Moreover, thanks to the feature that allows the virtual arm to be adjusted according to the patient’s motor abilities, it is possible to generate an augmented movement even if the patient has minimal ability. Moreover, in contrast to traditional rehabilitation programs, VR treatments are typically well-received by patients due to their immersive environment and increased flexibility in catering to the patient’s clinical characteristics and progress. Additionally, patients have the opportunity to track and record their motor performance [30, 67].

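### Hypothesis 1 claims equal motor effectiveness, but the sample size and the only test of motor change address a difference, with no margin, and the Discussion states superiority instead

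*Protocol article*

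**What the plan says.** Section 2 of the protocol article separates two kinds of claim. For motor ability (2.1), "VR rehabilitation programs will generally be as effective as TAU in increasing the motor abilities of the injured upper limb after a stroke". For proprioception (2.2), "The VR rehabilitation program will be more effective than TAU in the proprioception abilities of the injured upper limb". The change from an equality claim to a superiority claim within one section suggests that the difference is meant.

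Section 3.5.1 names a motor measure as primary: "The primary outcome measures will be the Fugl-Meyer for Upper Limbs", scored 0 to 66.

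Section 3.5.3 sets 30 participants per group from a G*Power repeated-measures ANOVA, with effect size 0.2, α 0.05, power 0.80 and 20% attrition.

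Section 3.7 says that changes in motor performance and proprioception "will be assessed using the repeated measures Analysis of Variance (rmANOVA) with a mixed design 2×3", at α 0.05, with a 95% confidence interval for each estimate. It names no equivalence or non-inferiority test and no margin.

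Section 4 gives the central hypothesis as VR increasing motor facilitation, which would in turn "improve upper limb control and function compared to the control condition".

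**The concern.** A claim of equal effectiveness needs a stated amount of inferiority (or difference in either direction) that the data can rule out. The planned F tests have no difference as their null hypothesis. Rejecting the null shows a difference. Failing to reject it does not show equality, least of all in a trial of this size. Hypothesis 1 therefore has no test attached to it.

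Hypothesis 1 and the Discussion also make different claims about motor ability. Until they are reconciled, it is unclear which finding on the Fugl-Meyer would count as success. The type of hypothesis and its margin determine the design and the number of patients. This is therefore more than a detail commonly left to an analysis plan.

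**Working it through.** **1. The plan's own sample size.** I read the effect size 0.2 as Cohen's f and the tested effect as the group-by-time interaction with three occasions and sphericity. Both are assumptions. The formula is λ = f²·N·m/(1−ρ), with degrees of freedom 2 and 2(N−2).
- At ρ = 0.5, 80% power needs N = 42, and 42/0.8 = 52.5, so 53 in total.
- At ρ of about 0.43, N = 48, and 48/0.8 = 60, the stated total.

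The article does not give ρ, so 30 per group can be neither confirmed nor called wrong. Either way it is a number for detecting a difference. The 0.2 is an effect to find and not a margin to exclude.

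**2. What each result would mean for motor ability.**

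| Result of the planned test | Discussion (superiority) | Hypothesis 1 (equality) |
|---|---|---|
| Significant, VR better | supported | not equality; a stronger claim |
| Significant, VR worse | contradicted | contradicted |
| Not significant | not supported | not shown; no margin to judge it by |

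Only if Hypothesis 1 were read as at least as effective would the first row imply it, and then through superiority. The situation that Hypothesis 1 describes, similar recovery in both arms, is one that the test cannot establish.

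**3. Precision at one time point.** Completers per arm: 30 × 0.8 = 24. The half-width of the 95% interval for VR minus TAU, in SD of the analysed score, is t(0.975, 2n−2)·√(2/n).
- n = 24: 2.013 × √(2/24) = 0.58 SD
- n = 30: 2.002 × √(2/30) = 0.52 SD

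**4. Chance of a non-significant result if VR is truly worse (two-sample t-test at one time point).** The non-centrality is d·√(n/2).
- d = 0.5: 60% with n = 24, 52% with n = 30
- d = 0.3: 83% with n = 24, 79% with n = 30

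**5. The same question for the planned group-by-time test.** Assume no difference at T1, a sustained 0.5 SD deficit at T2 and T3, sphericity and 24 per arm. The between-arm differences (0, −0.5, −0.5) deviate from their mean by 1/3, −1/6, −1/6, and the squares sum to 1/6. Each arm carries half of each deviation, so λ = 48 × (1/4) × (1/6)/(1−ρ) = 2/(1−ρ), with degrees of freedom 2 and 92.

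| Within-patient correlation ρ | λ | Non-significant |
|---|---|---|
| 0 | 2.0 | 78% |
| 0.5 | 4.0 | 60% |
| 0.7 | 6.7 | 38% |
| 0.8 | 10.0 | 20% |

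**6. What a non-inferiority test could deliver.** Take one-sided 0.025 and a true difference of 0. The article gives neither an SD nor a margin, so margins are assumed in SD units.
- Power with 24 per arm (noncentral t): 27% for a 0.4 SD margin, 40% for 0.5 SD, 82% for 0.85 SD.
- The margin giving 80% power is about 0.81 SD with 24 per arm and 0.72 SD with 30, from the normal approximation.
- Completers per arm for 80% power, 2·((1.96+0.84)/margin)²: 63 for 0.5 SD (63/0.8, so 79 recruited) and 99 for 0.4 SD (99/0.8, so 124 recruited).

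Adjustment for baseline would reduce the relevant SD and so improve these figures, but it would not supply a margin.

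**The case against.** Four points can fairly be made for the plan.

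- **No stated rule that non-significance means equality.** A reader might infer that a non-significant F test will be reported as equal effectiveness. The article does not say this. What stands is narrower: no rule for Hypothesis 1 is given, and the named test cannot supply one.
- **Confidence intervals are promised.** Section 3.7 commits to 95% intervals, so the uncertainty would be visible. They can support equal effectiveness only against a margin fixed beforehand.
- **Hypothesis 1 may simply be loosely worded.** It is qualified as a general statement, speaks of motor abilities, and does not name the Fugl-Meyer. Box and Blocks is a motor measure too. No hypothesis is labelled primary, and the sample size and test both fit a difference design. This is plausible, and it would make the repair a rewording. The contradiction with the Discussion remains, and the Fugl-Meyer is the designated primary outcome.
- **A choice of hypothesis after the data are seen is conjecture.** A reader might infer that the two statements are there to allow it. Nothing in the article supports that.

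Section 3.5 also ties the minimal clinically important difference to the satisfaction questionnaire and describes the p-value as the probability that results are due to chance. Both deserve correction, but they would be faults whatever Hypothesis 1 said. They are secondary and are not relied on here.

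**Conclusion.** The point holds. Hypothesis 1 states equal effectiveness on motor ability, while the sample size and the only test named for motor change address a difference. With no margin or decision rule, no result of that test can support Hypothesis 1 as worded. The Discussion states a different hypothesis on the same ability, and the two must be reconciled.

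The size is illustrative. A true 0.5 SD disadvantage would often go undetected with 24 completers per arm: in 60% of trials at a single time point, and in 78% down to 20% with the group-by-time test, depending on a correlation that the article does not state. The 60% is therefore one point in a wide range. The conclusion itself rests on the text and not on these figures, nor on whether 30 per group can be reproduced.

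**What to change.** State one hypothesis for the Fugl-Meyer and use it in both section 2.1 and section 4.

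- **(a) Superiority.** Reword Hypothesis 1 so that VR is expected to do better than TAU. This fits the existing ANOVA and sample size. Add that a non-significant result will not be reported as equal effectiveness. The cost is wording only.
- **(b) Equal effectiveness.** Keep the claim and, before outcome data are seen, fix a justified margin in Fugl-Meyer points at T2. Claim Hypothesis 1 only if the lower 95% confidence limit of VR minus TAU lies above minus the margin. State the power at the planned size: with 24 per arm, about 27% for a 0.4 SD margin, 40% for 0.5 SD, and 80% only near 0.8 SD.

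Route (b) costs little to write, but the stated power is less favourable. Powering a 0.5 SD margin at 80% would need about 79 recruited per arm against the 30 planned. If the size stays as it is, Hypothesis 1 may have to be presented as an estimation aim.

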#### 3.5.3. Sample size

A sample size of 30 participants per group has been determined using G*Power 3.1.3. This calculation was based on a repeated measures ANOVAs (within and between subjects), considering a small to medium effect size of 0.2 [60], as also reported in a two-arm Randomized Control Trial involving chronic stroke participants that also adopted as primary outcome measure the Fugl-Meyer scale [61]. The sample size determination also accounted for 20% attrition, with a significance level (α) set at 0.05 and a desired statistical power of 0.80, as outlined in the literature [62]. Additional, participants will be enlisted in the event of any dropouts.

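### Hypothesis 1 claims equal motor effectiveness, but the planned test and power are for a difference, and no Fugl-Meyer margin or decision rule is stated

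*Protocol article*

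**What the plan says.** Section 2 of the protocol article separates two kinds of claim. For motor ability, Hypothesis 1 reads: "VR rehabilitation programs will generally be as effective as TAU in increasing the motor abilities of the injured upper limb after a stroke". For proprioception, Hypothesis 2 reads: "The VR rehabilitation program will be more effective than TAU in the proprioception abilities of the injured upper limb".

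Section 3.5.1 makes the motor scale primary: "The primary outcome measures will be the Fugl-Meyer for Upper Limbs". It lists assessments at T1, T2 and T3 and does not single out one as the primary time point.

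Section 3.7 names one method for the outcomes, the "repeated measures Analysis of Variance (rmANOVA) with a mixed design 2×3". The t-test and Mann-Whitney test are named for the baseline comparison only. On error rate and estimation it says "the probability of type 1 error is a-priori fixed at alpha α = 0.05 and will include reporting the 95% Confidence Interval for each estimate". The analysis set is per protocol.

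Section 3.5.3 gives 30 per group: "This calculation was based on a repeated measures ANOVAs (within and between subjects), considering a small to medium effect size of 0.2", with 20% attrition, alpha 0.05 and power 0.80.

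Section 3.5 describes a p-value below a threshold as statistical significance, names the confidence interval as a measure of precision, and ties the minimal clinically significant difference to the satisfaction questionnaire. The Discussion (section 4) states the central hypothesis as VR increasing motor facilitation and so helping to "improve upper limb control and function compared to the control condition".

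**The concern.** A claim that one treatment is as effective as another needs a statement of how large a deficit would still count as equal, and a rule for excluding anything larger. The plan has neither for the Fugl-Meyer. Its test has no difference as the null hypothesis, so a significant result in favour of TAU would speak against Hypothesis 1, and a non-significant result would leave it open. The power of 0.80 is the probability of finding a difference of the stated size, which is the opposite of what Hypothesis 1 asserts.

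At stake is the main conclusion of the trial. If the Fugl-Meyer comparison is not significant, the plan gives no basis for saying whether VR matches usual physiotherapy or whether the trial was too imprecise to tell.

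**Working it through.** **1. The passages side by side.**

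| Element | Where | Question it addresses |
|---|---|---|
| Motor hypothesis | 2.1 | Equal effectiveness |
| Proprioception hypothesis | 2.2 | Superiority |
| Primary outcome: Fugl-Meyer | 3.5.1 | Motor domain, so 2.1 applies |
| Outcome test: 2×3 ANOVA, alpha 0.05 | 3.7 | Is there a difference? |
| Sample size: effect 0.2, power 0.80 | 3.5.3 | Detecting a difference |
| Central hypothesis | 4 | Motor improvement over control |
| Fugl-Meyer margin | not stated | – |

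**2. The plan's own figure.** Take 0.2 as Cohen's f and use the group-by-time interaction with k = 2 groups, m = 3 measurements and sphericity: noncentrality λ = f²·N·m/(1 − ρ), degrees of freedom (m − 1) and (N − 2)(m − 1). The correlation ρ is not stated.

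- ρ = 0.5 (assumed): 42 evaluable patients in total are needed. 42/0.8 = 52.5, so 53 enrolled.
- ρ = 0.43 to 0.44: 48 evaluable are needed, and 48/0.8 = 60 enrolled, the stated total. At ρ = 0.43 and N = 48, λ = 0.04 × 48 × 3/0.57 = 10.1 and power is 0.81.
- The between-group main effect at ρ = 0.5 needs 134 evaluable.

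So 60 can be neither confirmed nor called wrong. Every setting found that reaches it is a test of a difference.

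**3. What this size can say about equal effectiveness (illustrative).** The protocol gives neither a margin nor a Fugl-Meyer SD, so margins are assumed in units of the SD of whatever is compared at one time point (score or change). Inputs: 30 per arm, or 30 × 0.8 = 24 after attrition. The standard error of the difference is √(2/n) SD.

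- 95% interval half-width = t(0.975, 2n − 2) × √(2/n). For n = 24: 2.013 × 0.2887 = 0.58 SD. For n = 30: 2.002 × 0.2582 = 0.52 SD.
- Power for non-inferiority (one-sided 0.025, true difference 0) is the chance that a noncentral t with noncentrality margin/√(2/n) exceeds the critical value.

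| Assumed margin | n = 24 | n = 30 |
|---|---|---|
| 0.3 SD | 17% | 21% |
| 0.4 SD | 27% | 33% |
| 0.5 SD | 40% | 48% |

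**4. How often a real deficit would be non-significant.** With the same single-time-point t-test, a true VR deficit of 0.5 SD gives p > 0.05 in 60% of trials (n = 24) or 52% (n = 30).

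For the planned 2×3 interaction, take a deficit of 0.5 raw-score SD at both T2 and T3, none at T1, N = 48 and sphericity. The centred differences have sum of squares 0.5² × 2/3 = 0.1667, so λ = (24/2) × 0.1667/(1 − ρ) = 2/(1 − ρ).

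| Assumed ρ | λ | Non-significant |
|---|---|---|
| 0.5 | 4.0 | 60% |
| 0.7 | 6.7 | 38% |
| 0.8 | 10.0 | 20% |

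The size of the problem thus depends on an unstated correlation.

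**The case against.** Four points can be made for the plan.

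*Confidence intervals are planned.* This stands in part. Section 3.7 promises a 95% interval for each estimate, and an interval is the right tool for a non-inferiority judgement. It would be wrong to say that nothing in the plan could carry Hypothesis 1. What is lacking is the margin and the rule. A rule could sit in an analysis plan that is not shown, but a margin would normally drive the sample size, and section 3.5.3 shows no such basis.

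*The Discussion states superiority.* This also stands. If the text is reconciled in that direction, test and power fit the hypothesis and the mismatch disappears. As it is written, the Discussion adds a contradiction with section 2.1 and does not resolve it.

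*Hypothesis 1 is loosely worded, and the trial never calls itself a non-inferiority or equivalence trial.* True, and rewording may be all that is needed. But section 2 uses different wording for proprioception, so the distinction looks deliberate.

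*The protocol does not say that a non-significant result will be read as equality.* Correct. A reader might infer it, because section 3.5 gives a rule only for significance, but no passage states it. The point here is that such a reading would be unsupported, not that the authors have planned it.

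**Conclusion.** The mismatch is in the text and does not depend on any assumed figure: Hypothesis 1 asserts equal motor effectiveness, while the test in 3.7 and the power in 3.5.3 concern detection of a difference. No Fugl-Meyer margin is stated, and the only minimal important difference mentioned concerns satisfaction. A non-significant ANOVA could not support Hypothesis 1, and the 0.80 power does not apply to it.

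The size is illustrative. For a single-time-point comparison, the interval half-width is 0.52 to 0.58 SD, and power to exclude a 0.5 SD deficit with equal arms is 40% to 48%. The margins are assumed, and the calculation is not the planned 2×3 ANOVA. Baseline adjustment or a high within-patient correlation would improve the precision by an amount the protocol does not allow one to state. The figures do not show that the sample size of 60 is wrong for its own purpose.

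**What to change.** Choose one of two repairs, both by wording.

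**A.** Reword 2.1 as superiority, or as estimation of the VR minus TAU difference with its 95% interval. Either is consistent with 3.5.3 and 3.7, and superiority also agrees with the Discussion. If estimation is chosen, align the Discussion with it.

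**B.** Keep equal effectiveness as the hypothesis, and align the Discussion with it. In 3.7, prespecify:
- a Fugl-Meyer margin in points, justified clinically and not derived from the number of patients available, and fixed before any outcome data are seen by arm (only the patient is described as blind, so unblinding is not a usable reference point);
- one primary time point;
- the rule that equal effectiveness is concluded only if the lower limit of the 95% interval for VR minus TAU lies above minus the margin;
- an analysis of all randomised patients to support the per-protocol result.

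In either case, state in 3.7 that p > 0.05 is not evidence of equal effectiveness. State in 3.5.3 that the 0.80 power is for detecting a difference, and report the expected precision of the Fugl-Meyer comparison.

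The cost is text in 2.1, 3.5.3, 3.7 and possibly the Discussion. The wording itself needs no extra patients or data, apart from what an all-randomised analysis needs from patients who drop out. The downside is that the trial may be able to support only an estimate of the difference, not a claim of equal effectiveness.
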